### Intervention

#### Training Intervention

For step monitoring, a wearable Xiaomi smart bracelet step tracker (*Smart Band 9 Active* model), validated for step tracking, will be used on the nondominant wrist for at least 12 hours a day [28]. Participants will receive physical activity goals based on adherence to international recommendations for steps per day (≥10,000 steps/d) [17,29,30].

A member of the research team will provide personalized feedback via email or WhatsApp (Meta Platform, Inc) daily, reinforcing achievements and adjusting goals when necessary. In addition, educational infographics designed to promote physical activity will be sent weekly, detailing the benefits of walking, strategies to increase the step counts, and practical recommendations for maintaining adherence (Figure 1). The weekly and total step records will be obtained through a downloadable CSV file from the Mi Fitness app (Xiaomi Mobile Software Co, Ltd), which will be downloaded by the user and sent to the research team via email.

**Figure 1 figure1:**
[figure not shown]
Group intervention activities.

#### Duration of the Intervention

The intervention will last 14 weeks. Initial assessments are scheduled to take place from March 2, 2026, to March 13, 2026. The intervention itself will be performed from March 16, 2026, to May 22, 2026. Final evaluations will be performed from May 25, 2026, to June 5, 2026. Inclusion and exclusion criteria, participant selection and randomization procedures, as well as baseline and follow-up assessments are summarized in the flowchart presented in Figure 2.

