**Results:**

The recruitment process will begin in March 2026. Initial assessments are scheduled to take place from March 2, 2026, to March 13, 2026. The intervention will be performed from March 16, 2026, to June 19, 2026 (14 weeks). From June 22, 2026, to July 6, 2026, the final evaluations will be performed. The final results of this study are expected to be published by October 2026.

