## Methods

### Design

It will be a 2-arm randomized controlled trial (RCT) to analyze a physical activity intervention in college students for 14 weeks. The RCT will be reported according to the CONSORT (Consolidated Standards of Reporting Trials) statement [25] and the SPIRIT (Standard Protocol Items: Recommendations for Interventional Trials) guidelines [26] (Multimedia Appendix 1).

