## Results

The project was awarded in April 2025. Subsequently, the project was reviewed for possible updates. In August 2025, funds were received, and the necessary materials for the execution of the project were purchased. Between September 2025 and December 2025, the staff in charge of the evaluations will be trained. The recruitment process will begin in March 2026. Initial assessments are scheduled to take place from March 2, 2026, to March 13, 2026. The intervention will be conducted from March 16, 2026, to June 19, 2026 (14 weeks). From June 22, 2026, to July 6, 2026, final evaluations will be conducted. The final results of the study are expected to be published by October 2026. The main results will be provided to the participants in a summarized way and will also be disseminated to the scientific community through participation in scientific events.

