## Discussion

### Anticipated Findings

Considering that there is currently a high number of inactive adults [7] and that sedentary behaviors predominate in university students’ daily lives due to academic demands—which is associated with damage to their health [13]—it is necessary to implement strategies to help address this problem. Interventions based on wearable technologies have shown increases in daily step counts and, to a lesser extent, activity intensity, with small to moderate effects and heterogeneity between populations [16,18,26]. These findings support the use of goals and objective monitoring as key components.

One option that has proven to be effective, low cost, and easy to implement is physical activity through walking, which is monitored by daily step trackers. However, most studies implementing this strategy have generated evidence by monitoring physical activity for 7 days on average [37], which could cause the reported results to be biased because participants could change their physical activity behaviors because they are aware that they are being evaluated [21]. This reinforces the need for research with longer follow-up periods that allow for a more detailed analysis of the relationship between daily steps and health indicators. In the university population, recent studies have shown that programs of 8 to 12 weeks supported by mobile apps and messaging can lead to significant increases in daily steps [21,22,25,27]. On the basis of this evidence, this protocol proposes a duration of 14 weeks, with individualized goals and weekly feedback, with the aim of achieving more sustained effects than those observed in interventions of shorter duration.

The choice of a long period is based on the need to assess the sustainability of change, given that recent reviews suggest that initial increases may decrease over time [5,20]. Likewise, setting explicit daily goals has been associated with higher levels of compliance, and more recent proposals even propose hourly objectives as a tactic to achieve the daily goal [17,29].

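### The Methods section on duration states 14 weeks but gives dates that span 10, and its final-evaluation window conflicts with the one in the Abstract and Results

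*Protocol article*

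**What the plan says.** The Protocol article gives the trial calendar in three places.

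- **Methods, Duration of the Intervention.** It opens with "The intervention will last 14 weeks". After the baseline assessment dates (March 2 to 13) it continues "The intervention itself will be performed from March 16, 2026, to May 22, 2026" and then "Final evaluations will be performed from May 25, 2026, to June 5, 2026".
- **Results section.** It reads "The intervention will be conducted from March 16, 2026, to June 19, 2026 (14 weeks", with the 14 weeks in parentheses directly after the dates, and then "From June 22, 2026, to July 6, 2026, final evaluations will be conducted".
- **Abstract, Results.** It gives the same intervention dates as the Results section, also labelled 14 weeks, and says "From June 22, 2026, to July 6, 2026, the final evaluations will be performed".

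The baseline assessment dates and the March 16 start agree in all three places. Only the intervention end and the final-evaluation window differ.

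Elsewhere the length is always 14 weeks. The Design section describes a trial "to analyze a physical activity intervention in college students for 14 weeks". The Abstract's Methods paragraph, Anticipated Findings and Conclusions also give 14 weeks. No sentence states 10.

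**The concern.** The section headed Duration of the Intervention is where site staff and later readers will look for the length of exposure and the timing of outcome measurement. Its dates fit neither its own opening sentence nor the other two calendars.

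Fitness, strength and body composition are measured only before and after the programme, so the final-evaluation window fixes when every post-intervention value is taken. A team working from the Methods dates would stop the programme and begin final testing while the schedule in the Abstract and Results still had four weeks to run.

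The length also carries the trial's rationale. Anticipated Findings notes that "recent studies have shown that programs of 8 to 12 weeks supported by mobile apps and messaging" have raised step counts, and justifies 14 weeks as a way to obtain more lasting effects than shorter programmes. A 10-week programme would sit inside that earlier range.

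**Working it through.** **Inputs.** All dates are in 2026 and come from the Protocol article.

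| Item | Methods, Duration of the Intervention | Abstract and Results |
|---|---|---|
| Intervention start | Mon March 16 | Mon March 16 |
| Intervention end | Fri May 22 | Fri June 19 |
| Final evaluations start | Mon May 25 | Mon June 22 |
| Final evaluations end | Fri June 5 | Mon July 6 |
| Stated length | 14 weeks | 14 weeks |

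**Step 1: reproduce the 14 weeks from the Abstract and Results dates.** Inclusive days = days in March + April + May + June = 16 + 30 + 31 + 19 = 96. In calendar weeks, 96 / 7 = 13.7. The span runs from a Monday to a Friday, so it holds 70 weekdays, and 70 / 5 = 14.0 weeks. The stated length is reproduced exactly when weeks are counted Monday to Friday.

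**Step 2: apply the same count to the Methods dates.** Inclusive days = 16 + 30 + 22 = 68. In calendar weeks, 68 / 7 = 9.7. This span too runs Monday to Friday and holds 50 weekdays; 50 / 5 = 10.0 weeks. Neither way of counting gives 14.

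**Step 3: size of the difference in exposure.**

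- Calendar days: 96 - 68 = 28, and 28 / 96 = 29%.
- Weekdays: 70 - 50 = 20, and 20 / 70 = 29%.

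**Step 4: the final-evaluation windows.**

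- Start: May 25 to June 22 is 28 days.
- End: June 5 to July 6 is 31 days. The extra 3 days arise because the later window closes on a Monday.
- The earlier window closes on June 5 and the later one opens on June 22, 17 days afterwards. They do not overlap, so both cannot be followed.

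**Step 5: what does not change.** The sample-size calculation uses a difference of 3, an SD of 5, α of .05 and power of .80; duration is not an input. The tests listed under Statistical Analysis do not depend on it either.

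**The case against.** The strongest reply is that the Methods paragraph can be made to add up. Two weeks of baseline assessment (March 2 to 13), ten of walking (March 16 to May 22) and two of final evaluation (May 25 to June 5) give 2 + 10 + 2 = 14 Monday-to-Friday weeks. The paragraph also distinguishes the intervention itself from the assessments around it. On that reading, 14 weeks covers the whole study, nothing is miscounted, and June 19 is only one possible correction.

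The sum is right, and it may well explain where the dates came from, though that is an inference. It does not rescue the text. The Abstract's Methods paragraph gives the walking programme itself as 14 weeks, and the Design section applies 14 weeks to the intervention. The Abstract and Results list the assessments separately and attach 14 weeks to the March 16 to June 19 dates alone. Even on the 2 + 10 + 2 reading, the Methods calendar would still conflict with the other two.

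Two parts of the reply stand. First, the consequences are limited. Both arms are assessed at the beginning and end of the programme, so either calendar gives a concurrent comparison. Second, a careful reader can work out the likely intent, which makes this a correction to the text and not a flaw in the design.

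**Conclusion.** The point holds. The Methods section on duration is wrong as written. Its dates give 10 weeks against a stated 14, ending the intervention and opening the final evaluations 28 days earlier than the Abstract and Results do.

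Taking June 19 as the intended end rests on the agreement of the Abstract and Results, on every stated length being 14 weeks, and on the June 19 date reproducing that length exactly. The week counts assume Monday-to-Friday weeks; by calendar weeks the figures are 9.7 and 13.7, and the conclusion is the same.

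This should be fixed because the paragraph governs exposure and endpoint timing. Power, analysis and the validity of the comparison between arms are not in question.

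**What to change.** In Methods, Duration of the Intervention, change three dates:

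- intervention end: May 22 to June 19, 2026;
- final evaluations start: May 25 to June 22, 2026;
- final evaluations end: June 5 to July 6, 2026.

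Check that any dates in Figure 2, which was not available for this review, agree with these. The cost is one corrected paragraph, with no change to design, sample size or analysis.

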**Figure 2 figure2:**
[figure not shown]
Recruitment, randomization, and evaluation flowchart.

#### Adherence to the Intervention Criteria

Those who make up the control group will also have their health indicators evaluated at the beginning and end of the intervention. Participants will also use the same *Xiaomi Smart Band 9* Active for at least 12 hours a day and will submit the weekly and total step log report, downloaded from the Mi Fitness app, to the research team. However, they will not receive specific step goals, individualized feedback, or behavior change strategies. They will maintain their usual physical activity habits without setting quantitative targets or providing personalized motivational messages.

### Procedures

Signed informed consent will be obtained once the sample has been recruited. Then, the evaluations of cardiorespiratory endurance, muscle strength, body composition, and the sociodemographic questionnaire will be scheduled. Subsequently, each participant will be given a step tracking device as well as training on their operation, maintenance, and how to download the step report from the Mi Fitness app.

### Measuring Health Indicators

#### Cardiorespiratory Fitness

This indicator will be measured through the 20-m shuttle run test [31]. Participants must run between 2 lines separated by 20 m. The speed at which they must move is indicated by a sound emitted by a recorded tape. The participant begins at a speed of 8.5 km/h, which increases by 0.5 km/h every minute. When a participant being evaluated fails to reach the lines twice in a row, along with the sound, or when they are unable to continue running the test, the evaluation is completed, and the minute reached is recorded. According to the proposal, the maximum oxygen consumption is estimated [31].

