### Sample Size Calculation

On the basis of what was proposed for the design of the RCTs [27], the number of participants will be calculated. Taking 2 RCTs that aimed to increase physical activity levels through walking [18,19] as reference, the sample will be calculated considering an absolute difference of 3% (α error of .05 and statistical power of .80) between the intervention group and the control group in the mean percentage of cardiorespiratory endurance (SD 5), giving a required sample of 99 participants for each group (intervention and control).

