### Statistical Analysis

The normality of the data will be checked through the Kolmogorov-Smirnov test, which will indicate the steps to be taken in relation to the comparison tests. Once the pretest tests have been performed, comparison analyses will be performed between groups (2-tailed Student *t* test or Mann-Whitney *U* test) to check the homogeneity of the groups. At the conclusion of the final evaluations of the study, intragroup differences will be analyzed using a statistical test of repeated measures (Student *t* test for related samples or Wilcoxon signed-rank test), along with the intergroup differences (Student *t* test or Mann-Whitney *U* test).

Cohen *d* will be used to determine the effect size on variables in which significant differences are found, using the following scale: 0.2 or greater=small, 0.5 or greater=moderate, and 0.8 or greater=large [33]. In addition, regression analyses will be performed incorporating the covariates. The simple imputation method will be used for all analyses [34], keeping the participants in the group to which they were assigned (intervention or control) regardless of the sessions they attended [35]. In valid cases, analyses will be performed to determine sensitivity [36]. For all tests, statistical significance will be set to *P*<.05. The data will be analyzed using SPSS statistics (version 29; IBM Corp).

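### The sample size rests on a percentage of cardiorespiratory endurance that the shuttle run section does not define, so the planned difference and power are not tied to the outcome analysed; recording laps would also sharpen the score

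*Protocol article*

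**What the plan says.** **Sample Size Calculation.** The trial is sized by "considering an absolute difference of 3"% between the groups "in the mean percentage of cardiorespiratory endurance (SD 5"), with "α error of .05 and statistical power of .80", "giving a required sample of 99 participants for each group (intervention and control"). The section gives no unit for the SD and no definition of the percentage.

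**Cardiorespiratory Fitness.** Fitness is measured once before and once after the intervention with the 20-m shuttle run. "The participant begins at a speed of 8.5 km/h, which increases by 0.5 km/h every minute". When the participant stops or twice in a row misses the line, "the evaluation is completed, and the minute reached is recorded". Maximum oxygen consumption is then estimated by a cited method; the article gives neither its equation nor its unit.

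**Statistical Analysis.** After the final evaluations, groups are compared with a t test or Mann-Whitney test, and pre-post differences within each group with a paired t test or Wilcoxon test. The t test is described as "2-tailed Student".

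**The concern.** A sample size calculation has a use after the trial only if its difference and SD are on the scale of the outcome analysed. Here the sizing names a percentage, and the test section names minutes and an oxygen consumption estimate. The only outcomes the article itself gives as percentages are adipose and muscle tissue, which are not fitness measures. A reader cannot say whether an observed difference reaches the one planned for, or whether an SD of 5 is reasonable.

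The recorded score also deserves a look. Speed rises once a minute, so if only the last minute is kept, a participant who gains several laps within the same minute is scored as unchanged. This loses precision that the test could supply at almost no cost, and laps not recorded at baseline cannot be recovered later.

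**Working it through.** **1. The plan's own figure.** Inputs from Sample Size Calculation: difference 3, SD 5 (taken to be in the same unit), alpha .05, power .80. Two-sided testing is taken from Statistical Analysis.

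n per group = 2 × (1.960 + 0.842)² × SD² / difference² = 2 × 7.849 × 25 / 9 = 43.6, so **44** (45 with the t distribution). The stated figure is 99.

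Other readings tried:

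| Reading | n per group |
|---|---|
| One-sided alpha .05, power .80 | 35 |
| Two-sided, power .90 | 59 |
| Two-sided, power .95 | 73 |
| Two-sided, power .99 | 103 |
| Two-sided alpha .01, power .80 | 65 |
| Both arms together, stated inputs | 88 in total |
| Difference 2, SD 5 | 2 × 7.849 × 25 / 4 = 98.1, so 99 |
| Difference 3, SD 7.5 | 2 × 7.849 × 56.25 / 9 = 98.1, so 99 |

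Reaching 99 from 44 by a dropout allowance would need a loss of 1 − 44/99 = 56%, and the section states no allowance. With 99 per group and the stated inputs, power is 98.8%, not 80%. The figure 99 fits a difference of 2 with SD 5, or 3 with SD 7.5. Without a defined unit, the article does not show which input is wrong.

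**2. Sized variable against measured variable.**

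| | Quantity | Unit |
|---|---|---|
| Sample Size Calculation | percentage of cardiorespiratory endurance | %, with no reference value |
| Cardiorespiratory Fitness, raw | minute reached | minutes |
| Cardiorespiratory Fitness, derived | estimated maximum oxygen consumption | not stated |

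The choice of unit matters. Read as minutes, a difference of 3 is three stages, or 3 × 0.5 = 1.5 km/h. Read as percentage change for someone who reaches minute 6 (an illustration), it is 0.03 × 6 = 0.18 min. These are very different targets.

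**3. Cost of whole-minute scoring.** The article does not say whether part-minutes are credited; this step assumes they are not.

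Laps per minute = speed × 1000 / 60 / 20: 7.1 at 8.5 km/h and 10.4 at 12.5 km/h.

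Rounding to one minute adds about 1/12 min² to the variance of one reading and 2/12 = 1/6 min² to that of a pre-post change. The documents give no SD in minutes, so these are assumed:

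| Quantity | Assumed SD (min) | Added variance |
|---|---|---|
| Final value | 2.0 | (1/12)/4 = 2% |
| Change | 1.5 | (1/6)/2.25 = 7% |
| Change | 1.0 | (1/6)/1 = 17% |
| Change | 0.7 | (1/6)/0.49 = 34% |

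Simulation with scores rounded down agrees: the variance of change went from 2.24 to 2.41, from 1.00 to 1.16 and from 0.49 to 0.66.

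**The case against.** Four objections deserve an answer.

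*A percentage could be computed.* Fitness is measured at both visits, so percentage change from baseline is available. This stands: the percentage is undefined, not impossible to derive. But the article does not say that percentage change is meant, and does not list it among the analyses.

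*Whole minutes is an inference, and scoring detail may sit in a fuller protocol.* This also stands in part. The wording does not exclude credit for part-minutes, so the scoring point is a conditional improvement and not a demonstrated error. The objection does not reach the sizing point, because the article states both the sizing variable and the test result, and they do not match.

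*The scoring cost is small where it counts.* The between-group test follows the final evaluations and no change-score comparison between groups is stated. If final values are compared, the relevant figure is about 2%. The larger figures apply to within-person change and rest on assumed SDs.

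*One stage is larger than 3%.* A reader might infer that the test is too coarse for the difference sought, since 0.5 km/h is 5.9% of speed at 8.5 km/h and 4.0% at 12.5 km/h. The documents do not support this. Those are relative steps in one person's speed, while the plan states an absolute difference between group means on an undefined scale. Nor does a coarse score hide a mean difference. In simulations with assumed steps of 3.03 to 5.88 units, a true difference of 3 was recovered as 2.99 to 3.00, and power with 99 per group was 97.8% to 98.6%, against a calculated 98.8% without rounding.

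**Conclusion.** The point holds in two parts of unequal weight.

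The main part needs no assumption about scoring: the sizing variable is not an output of the fitness test as described, and no section links them. The stated difference, SD and power therefore cannot be set against the trial's result. The stated inputs also give 44 per group (two-sided, SD in the same unit as the difference), not 99. This does not show that the trial is too small. On the stated inputs, 99 is more than enough; what is missing is a justification that can be checked.

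The lesser part is a cheap gain in precision: about 2% of variance for final values and 7% to 34% for within-person change, given whole-minute scoring and the assumed SDs. That one stage exceeds 3% is not itself a flaw.

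**What to change.** In Sample Size Calculation, name the fitness outcome that will be analysed and give the planned difference and SD in its unit (laps, minutes or mL/kg/min), with their source. Then recompute the required number, or keep 99 per group and state the power it gives. Changing the unit alone is not enough, because the present inputs do not lead to 99.

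In Cardiorespiratory Fitness, record the completed 20-m laps (last minute plus laps within it) at both visits, and say how an unfinished minute enters the analysed score and the oxygen consumption estimate.

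The cost is a short revision with one recalculation, and one extra number on the test form, with no added staff or procedure. The scoring rule should be settled before the initial assessments, which the article schedules from March 2, 2026.

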#### Upper Body Muscle Strength

Using a digital dynamometer (Takei T.KK.5401; Takei Scientific Instruments Co, Ltd), grip strength will be evaluated. For each hand, the average of 2 measurements will be calculated.

